No more than 6 patients (3 + 3 patients) will receive the same dose during the dose escalation phase according to the following rules.Dose escalation to the subsequent cohort is possible if there is no DLT and no significant TET.If 1 DLT occurs, the ongoing cohort will be stopped, and another three patients will receive the next lower dose level tested, if only 3 patients have received this lower dose. If already 6 patients have received this lower dose, this lower dose represents MTD. If DLT occurs in cohort 1, the dose will be reduced to 4’200 mg/m^2^ weekly (ie. to 75 %), and this dose will be tested in 3 patients.If a 1-2 significant TETs occur, another three patients will receive the same dose.If out of 6 patients with the same dose, 3 or more significant TETs occur, this dose level will be the MTD.If out of 6 patients, 1-2 experience significant TETs, the dose may be increased to the next dose escalation step as shown in Table 1 in 3 additional patients. However, if a DLT has been observed, this dose must not be administered again.

Following these rules, a maximum of 48 patients are included in the dose escalation phase of the study. As soon as the MTD during the “dose escalation” phase is defined, a “dose extension” is performed in additional 21 subjects, who will receive the MTD.

In parallel, a maximum of three patients receiving the same dose of the IMP will be included in the study. Depending on the safety and tolerability of the compound, the next patient (or maximal the next three patients) who receives a higher dose, will be included after the last patient completed the whole IMP cycle (with a total of 9 applications) receiving the last lower dose.

A classical 3 + 3 phase I design was chosen for the dose escalation part of the study, because there is insufficient information on safety and tolerability of doses above 5’600 mg/m^2^ once weekly and of repeated doses in humans (unpublished data obtained from Normoxys®). This design induced the least toxicities in a simulation study comparing various dose finding escalation strategies and therefore appears to be most appropriate for a study using such substance in terminally ill cancer patients, where the therapeutic benefit is yet unknown.

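### After a DLT in cohort 1, the fallback dose of 4'200 mg/m² weekly is tested in only 3 patients, and the rules can be read to open the 21-patient extension on a clean 0/3

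*Protocol article*

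**What the plan says.** All the rules are in the protocol article, under Dose escalation and extension.

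- **DLT in cohorts 2–8:** "another three patients will receive the next lower dose level tested, if only 3 patients have received this lower dose". If six have already been treated there, "If already 6 patients have received this lower dose, this lower dose represents MTD".
- **DLT in cohort 1:** "the dose will be reduced to 4’200 mg/m^2^ weekly (ie. to 75 %), and this dose will be tested in 3 patients". The rule ends there.
- **TETs:** "If a 1-2 significant TETs occur, another three patients will receive the same dose". The other rule that names an MTD is "If out of 6 patients with the same dose, 3 or more significant TETs occur, this dose level will be the MTD".
- **No return to a toxic dose:** "However, if a DLT has been observed, this dose must not be administered again".
- **Limit per dose:** "No more than 6 patients (3 + 3 patients) will receive the same dose during the dose escalation phase".
- **Ceiling:** "Following these rules, a maximum of 48 patients are included in the dose escalation phase of the study".

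The MTD definition earlier in the same section takes the dose before the level at which one patient has a DLT, or the level with three or more significant TETs. It gives no minimum number of patients. The 21-subject extension starts once the MTD has been defined.

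**The concern.** The protocol asks for the least evidence where caution should be greatest. On this branch the starting dose, 5'598 mg/m² weekly, has already caused a DLT. The fallback is only 25% lower, and no earlier cohort in this trial stands behind it. The article itself justifies the 3 + 3 design partly by the lack of human data on repeated dosing, and 4'200 mg/m² weekly is a repeated-dose schedule.

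If three clean patients are enough, the dose given to 21 further patients rests on half the number that the protocol uses after a DLT in any other cohort.

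**Working it through.** **The plan's own figures.** Eight Table 1 cohorts × 6 patients = 48, the stated maximum, and 48 + 21 = 69. The step-down also agrees: 4'200 / 5'600 = 0.75 (4'200 / 5'598 = 0.750).

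**Which rule applies after 0/3 DLT and 0/3 TET at 4'200?**

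| Possible route to six patients | Does a clean 0/3 trigger it? |
|---|---|
| Same-dose expansion | No. It needs 1–2 significant TETs. |
| Filling the next lower tested dose after a DLT | Not clearly. It acts when the DLT occurs, and nobody has then received 4'200. |
| Six per dose | No. It is a maximum, not a minimum. |
| Escalating back to 5'598 | Barred, because a DLT occurred there. |

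No rule requires more patients, so the MTD definition is what remains. The rules also give no outcome for a DLT at 4'200, below which no dose exists.

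**Upper bounds.** After zero DLTs in n patients, the one-sided 95% upper bound is 1 − 0.05^(1/n).

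- n = 3: 1 − 0.05^(1/3) = 0.632
- n = 6: 1 − 0.05^(1/6) = 0.393

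**Operating characteristics.** The article gives no DLT or TET rates, so these are assumed: p is the DLT rate and q the TET rate per patient, mutually exclusive, with independent patients.

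- Clean 0/3: (1 − p − q)³
- Passes under the current rule: (1 − p − q)³ + [(1 − p)³ − (1 − p − q)³ − q³] × (1 − p)³. The second term covers 1–2 TETs followed by three DLT-free patients. Three TETs in the first three are left out (q³ is at most 0.008 here).
- Passes if six DLT-free patients are required: (1 − p)⁶

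Worked example, p = 0.2 and q = 0.1: the clean term is 0.7³ = 0.343. The second term is (0.512 − 0.343 − 0.001) × 0.512 = 0.086. The sum is 0.429, against 0.8⁶ = 0.262.

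| p | q | Clean 0/3 | Passes, current rule | Passes, six DLT-free |
|---|---|---|---|---|
| 0.1 | 0 | 0.729 | 0.729 | 0.531 |
| 0.1 | 0.1 | 0.512 | 0.669 | 0.531 |
| 0.1 | 0.2 | 0.343 | 0.619 | 0.531 |
| 0.2 | 0 | 0.512 | 0.512 | 0.262 |
| 0.2 | 0.1 | 0.343 | 0.429 | 0.262 |
| 0.2 | 0.2 | 0.216 | 0.363 | 0.262 |
| 0.3 | 0 | 0.343 | 0.343 | 0.118 |
| 0.3 | 0.1 | 0.216 | 0.259 | 0.118 |
| 0.3 | 0.2 | 0.125 | 0.197 | 0.118 |

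**Chance of the whole path.** A DLT in the first three of cohort 1 and then a clean 0/3 at 4'200, with the same rates at both doses, has probability [1 − (1 − p)³] × (1 − p − q)³.

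- p = 0.1: 0.198, 0.139 and 0.093 for q = 0, 0.1 and 0.2
- p = 0.2: 0.250, 0.167 and 0.105
- With q = 0 and lower DLT rates: 0.143 × 0.857 = 0.12 at p = 0.05, and 0.059 × 0.941 = 0.06 at p = 0.02

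**The case against.** The strongest reply is that the harm is inferred. No sentence calls 4'200 the MTD after 0/3. The dose is not in Table 1, and it is given after cohort 1, so it is not plainly the preceding dose. The three patients may simply be the usual first cohort of a 3 + 3: every cohort starts with three, and in later cohorts the step after a DLT also treats three new patients. Once treated, 4'200 could count as a tested lower dose with only three patients. Assessment of primary outcome also describes a decision after each patient on adding to the cohort or moving on. A condensed article may leave the next step to the full protocol.

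The ordinary reading is possible, so the claim is limited to what the text allows. But that reading still does not say what follows 0/3, and the decision after each patient permits continuing without requiring six. The article is not merely silent: it states a number, 3, that departs from its own practice elsewhere.

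Two further points stand in part. The dose is low: 4'200 is below the 5'600 mg/m² once-weekly level above which the article calls human data insufficient, and a thrice-weekly split would give 4'200 / 3 = 1'400 mg/m² per infusion. The reservation about repeated dosing still applies. Also, DLT rates of 10–30% have no anchor in the article. Lower rates make the path less likely, but they do not affect the comparison of 3 with 6 patients.

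**Conclusion.** The concern holds, as a weak safety rule in one conditional branch. The difference between cohort 1 and cohorts 2–8 is explicit. That the extension can open on 0/3 is a permissible reading, not a stated rule.

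The bounds of 63% and 39% depend only on the sample sizes. The pass probabilities and the chance of reaching this path depend on the assumed DLT and TET rates. The gap is confined to the clean 0/3 result, because 1–2 TETs already take the dose to six. The sponsor should change the rule, since the change is cheap and comes before 21 more patients are dosed.

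**What to change.** Replace the three-patient test at 4'200 mg/m² weekly with 3 + 3, so that six patients without a DLT are needed before this dose can be declared the MTD. In the same rule, state that a DLT at 4'200 means that no MTD is established and the extension does not open.

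**Cost in patients.** At most three more, within the existing limit of six per dose. If de-escalation starts from cohort k, the path total is at most 6k + 6, against 6k + 3 now on the clean path:

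- k = 1: 12 against 9
- k = 2 (cohort 1 re-entered after a DLT in cohort 2): 18 against 15
- k = 7: 48 against 45
- k = 8: 54 against 51

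Only the full cascade from cohort 8 passes 48, and the current rule already does so there. It needs each of cohorts 1–7 to have no DLT in its first three (probability x) and then one in the added three (1 − x). Since x(1 − x) ≤ 0.25, its probability is at most 0.25⁷ = 1/16,384, with independent patients.

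**Cost in lost doses.** The stricter rule also rejects tolerable doses more often. At a 10% DLT rate and no TETs, the chance that 4'200 passes falls from 73% to 53%, and each extra failure ends without an MTD. That is a reasonable price after a DLT at the starting dose, but the sponsor should accept it knowingly.

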### Dose escalation and extension

The aim of the escalation study part is the assessment of additional preliminary safety and tolerability data for the MTD. Safety will be assessed according to the (Common Terminology Criteria for Adverse Events (CTCAE), also known as common toxicity criteria (CTC). These criteria are issued by the US National Cancer Institute for the standardized classification of adverse effects of drugs used in cancer therapy. Specific symptoms and conditions define each level of this classification system ranging from 1-5, where 1 is the mildest form of the specific symptom and 5 is death. The CTCAE version used for this study will be version 4.03.

According to CTCAE, Dose Limiting Toxicity (DLT) will be defined as:any grade 5 toxicityany grade 4 neutropenia lasting >7 daysany grade 3 febrile neutropenia, thrombocytopenia, or anemiaany grade 3 or 4 nonhematologic toxicity, excluding alopecia, that is considered by the investigator to be definitely, probably or possibly related to OXY111A.

A significant Treatment-Emergent Toxicity (TET) is defined as any other grade 2 toxicity considered by the investigator to be definitely, probably, or possibly related to OXY111A, but not fulfilling the criteria for DLT.

Based on the assessment of DLT and TET the MTD will be noted. MTD is defined as the dose preceding the dose level at which one patient in the cohort experiences a DLT during the treatment cycle, or the dose level at which 3 or more patients experience a significant TET.

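### The six-patient MTD rule counts toxicities, but the MTD definition and the escalation rule count patients, and they disagree when 3 TETs fall in 2 of 6 patients

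*Protocol article*

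**What the plan says.** All the relevant text is in the protocol article, *Dose escalation and extension*.

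- **What a TET is.** A significant TET "is defined as any other grade 2 toxicity considered by the investigator" to be at least possibly related to OXY111A and not meeting the DLT criteria. The unit is a toxicity.
- **MTD definition (before Table 1), TET part.** "or the dose level at which 3 or more patients experience a significant TET". The unit is patients.
- **Rule for adding three patients (after Table 1).** "If a 1-2 significant TETs occur, another three patients will receive the same dose". The unit is TETs.
- **Stopping rule at six patients.** "If out of 6 patients with the same dose, 3 or more significant TETs occur, this dose level will be the MTD". The unit is TETs.
- **Escalation rule at six patients.** "If out of 6 patients, 1-2 experience significant TETs, the dose may be increased to the next dose escalation step". The unit is patients.

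Each patient is observed over a full cycle: the next dose opens only after the last patient on the lower dose has "completed the whole IMP cycle (with a total of 9 applications"). *Assessment of primary outcome* names establishing the MTD as part of the primary outcome, and the 21 extension patients are to be treated at that dose.

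**The concern.** The stopping rule and the escalation rule are meant to be complementary: three or more stops, one or two may go on. They are complementary only if both count the same thing. As written, one counts events and the other counts people. A patient with two different grade 2 toxicities contributes two TETs to the first count and one patient to the second, even if recurrences of the same toxicity are ignored.

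When the counts part, the same data support two decisions on the primary outcome. Counting events fixes the extension dose at a level that the definition does not call the MTD. Counting patients allows a new cohort to be treated above a dose that the stopping rule has just declared to be the MTD.

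**Working it through.** **Inputs.** From *Dose escalation and extension*: eight dose levels (Table 1), at most 6 patients per level, 9 applications per patient, and the rules quoted above. No TET rate is given anywhere in the document.

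**The plan's own figure.** 8 levels × 6 patients = 48, the stated maximum for the escalation part. It reproduces.

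**A reachable case.** One of the first three patients has 1 TET, so three more are added. One of those three has 2 TETs. There is no DLT. Total TETs E = 1 + 2 = 3; affected patients A = 2.

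| Sentence | Test | Result |
|---|---|---|
| Stopping rule | E ≥ 3 | 3 ≥ 3: this dose is the MTD |
| Escalation rule | A is 1 or 2 | 2: the dose may be increased |
| MTD definition | A ≥ 3 | 2 < 3: not the MTD |

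**All conflict cases.** The sentences disagree exactly when E ≥ 3 and A ≤ 2. Three or more affected patients necessarily have three or more TETs, so the conflict never runs the other way.

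- At most 1 TET per patient: E = A, so there are no conflict states.
- At most 2 TETs per patient, with the rule for adding three patients read as counting TETs: there must be one affected patient in each set of three. That gives 3 × 3 = 9 positions, times the TET pairs (1,2), (2,1) and (2,2), so 9 × 3 = 27 ordered states. Of these, 18 have E = 3 and 9 have E = 4.
- The same with that rule read as counting patients: two affected among the first three is now also possible. That adds 3 × 3 = 9 states, for 36 in all (24 with E = 3, 12 with E = 4).

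These are counts of states, not probabilities.

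**Illustration 1, conditional.** Take one affected patient in each set of three, each with 1 or 2 TETs. Let m be the assumed share of affected patients who have 2. The sentences disagree unless both have 1, so P = 1 − (1 − m)².

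| m (assumed) | P(disagree) |
|---|---|
| 0 | 0 |
| 0.10 | 1 − 0.81 = 0.19 |
| 0.25 | 1 − 0.5625 = 0.44 |
| 0.50 | 1 − 0.25 = 0.75 |

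**Illustration 2, per six-patient level.** Let p be the assumed chance that a patient has at least one TET, with independent Poisson counts per patient, so λ = −ln(1 − p). P(A ≥ 3) is the binomial tail for n = 6, and P(E ≥ 3) is the Poisson tail with mean 6λ. Their difference is the chance of conflict, taken from unrounded values.

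| p (assumed) | P(A ≥ 3) | P(E ≥ 3) | Conflict |
|---|---|---|---|
| 0.1 | 0.016 | 0.026 | 0.011 |
| 0.2 | 0.099 | 0.152 | 0.053 |
| 0.3 | 0.256 | 0.361 | 0.105 |
| 0.4 | 0.456 | 0.591 | 0.136 |
| 0.5 | 0.656 | 0.784 | 0.128 |

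This ignores clustering of TETs within patients and the condition that the first three patients led to three more being added.

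**What lies above the stopped dose.** From the weekly doses in Table 1, the seven steps are 100.0%, 50.1%, 25.0%, 25.0%, 20.0%, 18.0% and 17.0%. These are sizes of the step that would be forgone or taken, not an effect of the wording.

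**DLT rules.** They mix units in the same way: "If 1 DLT occurs, the ongoing cohort will be stopped" against "at which one patient in the cohort experiences a DLT during the treatment cycle". At a threshold of one, at least one event and at least one patient are the same condition, so no decision changes. At a threshold of three they are not.

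**The case against.** The strongest reply is that the document already shows what is meant. The formal definition counts patients. The stopping rule opens with a denominator of six patients, and it complements the escalation rule only if both count patients. On that view TETs is shorthand for patients with a TET, and a full protocol may well state a once-per-patient convention. As to intent this is persuasive, and patients are very probably the intended unit. It does not repair the sentence: the operating rule on the page has a threshold that differs from the definition, which is a conflict and not an omitted detail.

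Other points limit the consequence, and they stand:

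- The stopping sentence is mandatory and the escalation sentence is permissive, so stopping at 3 TETs in 2 patients breaches neither. The hard mismatch is between the stopping rule and the MTD definition.
- The literal rule errs towards caution. It stops earlier and exposes nobody to a higher dose; its possible cost is a lower extension dose.
- The final MTD may be the same either way. If the next level produces a DLT, the lower dose becomes the MTD because six patients have already received it. At cohort 8, Table 1 has no next level.
- No TET rate is available, so neither illustration measures how often the problem would arise.

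These points bear on how often the fault would matter. They do not remove it.

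**Conclusion.** The concern holds, as a misworded decision rule that should be corrected. At a six-patient dose level with three or more TETs in one or two patients and no DLT, the stopping rule declares an MTD that the formal definition does not. In the case worked through, escalation stops with 2/6 = 33% of patients affected, where the definition requires 3/6 = 50%.

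This rests on one reading: that two different grade 2 toxicities in one patient are two TETs, which follows from the TET definition. The frequency is unknown. It is zero if no patient has more than one TET, and about 1% to 14% per six-patient level under the Poisson assumption for p from 0.1 to 0.5. No stated figure is wrong, and the design itself is not in question.

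**What to change.** In the rule list after Table 1, count patients with at least one significant TET throughout. In the absence of a DLT:

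- 1 or 2 of the first 3 patients affected: add three patients at the same dose.
- 3 or more of up to 6 patients affected: this dose is the MTD. This includes 3 of the first 3, which the MTD definition already covers.
- 1 or 2 of 6 patients affected: the dose may be increased to the next step.

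The first rule needs the change as well as the second. Read as events, 3 TETs in 2 of the first 3 patients fits neither the rule for adding patients nor the six-patient rules.

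The cost is a wording amendment. There are no new procedures and no extra patients: the maximum remains 8 × 6 = 48.

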## Methods/Design

### Study design

This is a phase Ib/IIa dose escalation and extension study on the effects of OXY111A in patients suffering from primary and secondary hepato-pancreato-biliary or gastrointestinal malignancies not curable by surgical means.

The study design is exploratory, prospective, open-labelled and mono-centric. The study is divided in a dose escalation part with a maximum of 48 subjects and an extension part, in which 21 subjects will be included (specifically 4 dose expansion groups of 6 patients each determined by histology). Overall duration of an individual subject’s participation in the study is minimum 4 and maximum 9 weeks (Fig. 2).

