There are two factors to be considered for the OXY111A dose escalation part of this study: total dose administered and infusion rate. The human equivalent dose-corrected No Observed Adverse Effect Level (NOAEL) in rats was 15’000 mg/m^2^ once a week for 5 weeks, while it was 43’750 mg/m^2^ in minipigs also once weekly (unpublished data obtained from Normoxys®). From animal studies, hypernatremia is known to be associated with high plasma concentrations typically encountered at the end of the OXY111A infusion and probably associated with infusion rate. Therefore, infusion rates of not more than 750 mg/m^2^/min are recommended. According to available phase I data in healthy volunteers (unpublished data obtained from Normoxys®), cohort 1 starts at a dose close to 5’600 mg/m^2^ weekly, i.e. 1866 mg/m^2^ thrice weekly. Dose escalation is performed according to the following scheme up to a maximum calculated dose of 43’700 mg/m^2^ weekly, which corresponds to the NOAEL level administered once weekly in minipigs.

Table 1 schedules dose escalation. In each cohort, 3 patients will be included (Table 1).

**Table 1 Tab1:** Dose escalation scheme

Cohort No.	Weekly Dose	Single Dose	Total Dose (9 applications )	% Dose Escalation
1	5'598 mg/m^2^	1'866 mg/m^2^	16'794 mg/m^2^	baseline
2	11'196 mg/m^2^	3’732 mg/m^2^	33'588 mg/m^2^	100 %
3	16'800 mg/m^2^	5‘600 mg/m^2^	50‘400 mg/m^2^	50 %
4	21‘000 mg/m^2^	7‘000 mg/m^2^	63‘000 mg/m^2^	25 %
5	26‘250 mg/m^2^	8‘750 mg/m^2^	78‘750 mg/m^2^	25 %
6	31‘500 mg/m^2^	10‘500 mg/m^2^	94‘500 mg/m^2^	20 %
7	37‘170 mg/m^2^	12'390 mg/m^2^	111‘510 mg/m^2^	18 %
8	43'500 mg/m^2^	14'500 mg/m^2^	130'500 mg/m^2^	~17 %

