### Assessment of primary outcome

The primary outcome, safety and tolerability (establishing MTD) of the investigational medical product (IMP) will be assessed at every application for each patient. According to the 3 + 3 dose escalation schedule, after each patient, a decision on the continuation will be taken, i.e. to either add an additional patient in the same cohort or to continue with the next cohort after three patients.

Assessment will be done using CTCAE. The obtained data will be added to the electronic case report form (eCRF) using the software secuTrial® (interActive Systems GmbH (iAS), Berlin/Germany).

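### The next dose level may open before a grade 4 neutropenia that began in the last week of the cycle can be classified as a DLT

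*Protocol article*

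**What the plan says.** All the rules at issue except the assessment schedule and the participation time stand in the protocol article under Dose escalation and extension.

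- **When the next level may open.** Entry at a higher dose is subject to a general safety and tolerability proviso. Such patients, three at most, "will be included after the last patient completed the whole IMP cycle (with a total of 9 applications) receiving the last lower dose". No interval after the ninth application is given.
- **What must be absent.** "Dose escalation to the subsequent cohort is possible if there is no DLT and no significant TET".
- **DLT.** Four groups of events are listed. Only grade 4 neutropenia has a duration condition: it must last more than 7 days.
- **Significant TET.** This covers related grade 2 toxicity that does not meet the DLT criteria.
- **Counting period.** The MTD is the dose below the level at which "one patient in the cohort experiences a DLT during the treatment cycle", with a second branch based on TETs. The cycle is not given in days.
- **Schedule.** Cohort 1 receives "1866 mg/m^2^ thrice weekly", and Table 1 bases the total dose on 9 applications.
- **Assessment.** Under Assessment of primary outcome, safety and tolerability "will be assessed at every application for each patient".
- **Time in study.** Under Study design, a subject's "participation in the study is minimum 4 and maximum 9 weeks". The article does not say how this time divides between screening, treatment and follow-up.

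**The concern.** A rule that depends on DLT status needs that status to be known when the rule is applied. A toxicity that becomes a DLT only after more than a week at grade 4 cannot be read out on the day the cycle ends if it began a few days earlier. The TET category does not catch it in the meantime, because TET stops at grade 2. A patient with a severe, ongoing event can thus count as having no DLT and no TET for that event.

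The stakes are higher than in a design that tolerates one DLT in six. Here a single DLT stops the cohort and bars the dose. The next group could start at a dose up to 100% higher (cohort 1 to 2 in Table 1) while a DLT that would have prevented this is still developing. The article itself gives the lack of human data on higher and repeated doses as its reason for choosing a cautious 3 + 3 scheme. It is also unclear whether an episode that starts within the cycle but passes 7 days after it counts towards the MTD.

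**Working it through.** **Step 1. Cycle length from Table 1.**

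- Applications per week = weekly dose / single dose. Cohort 1: 5598 / 1866 = 3. Cohort 8: 43500 / 14500 = 3.
- Applications per cycle = total dose / single dose. Cohort 1: 16794 / 1866 = 9. Cohort 8: 130500 / 14500 = 9.
- Weeks = total dose / weekly dose. Cohort 1: 16794 / 5598 = 3. Cohort 8: 130500 / 43500 = 3.

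All eight cohorts give 3, 9 and 3. The stated maximum of 48 patients also reproduces, as 8 levels × 6 patients.

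**Step 2. Which onset days can be classified at opening.** Let E be the earliest day the next level may open and d the day of onset. The episode can be classified as a DLT by day E only if d + k ≤ E. Here k = 7 if the seventh day after onset is enough, and k = 8 if seven full days must be exceeded. Onsets with d + k > E are undetermined.

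The weekdays of dosing are not stated, so three readings were tried:

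| Reading (assumption) | E | Undetermined onsets, k = 7 | Undetermined onsets, k = 8 |
|---|---|---|---|
| Monday/Wednesday/Friday dosing, opening at the ninth application | 19 | days 13–19 (7 days) | days 12–19 (8 days) |
| Three consecutive days each week, opening at the ninth application | 17 | days 11–17 (7 days) | days 10–17 (8 days) |
| Cycle read as a full 3 weeks | 21 | days 15–21 (7 days) | days 14–21 (8 days) |

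The undetermined stretch is 7 to 8 days under every reading. It contains the last 3 or 4 of the 9 applications.

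**Step 3. The rules applied to one case.** Take Monday/Wednesday/Friday dosing and an afebrile grade 4 neutropenia with onset on day 15.

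- On day 19 it has lasted 19 − 15 = 4 days, so it is not a DLT.
- It is grade 4, so it is not a TET.
- For this event the condition of no DLT and no TET is met, and the cycle is complete. A higher dose may start.
- If the episode persists it becomes a DLT on day 22 or 23 (15 + 7 or 15 + 8), when up to three patients may already be on the next dose.

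**Step 4. Who and what is affected.** The overlap always concerns the last patient of the group. It extends to as many as three if the group is treated in parallel, which the article allows. The other DLTs (grade 5 events; grade 3 febrile neutropenia, thrombocytopenia or anemia; related grade 3 or 4 nonhematologic toxicity) have no duration condition and can be classified at onset.

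**The case against.** The strongest reply is that completing the cycle is only the earliest permitted time. The sentence opens with a safety and tolerability proviso and says after completion, so a team that sees an ongoing grade 4 neutropenia may wait. This stands as a limit: the text does not open the next level automatically at the ninth application, and a reader should not infer that it does. But the proviso names no duration and does not require DLT status to be settled, so it permits a wait without ensuring one.

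A second reply is that a condensed article leaves the exact DLT window and visit schedule to the full protocol. That would answer a complaint that a window is missing. Here, however, the article itself states the trigger, the counting period and the 7-day condition, and these do not fit together at the earliest opening time.

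A third reply is that the practical risk may be small. The toxicity the article names is hypernatremia around the end of infusion, and it describes the half-life as short. That may be so, but no neutropenia rate is given, and the plan itself lists this event as a DLT.

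Three stronger readings are tempting and not supported:

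- **All toxicity after the ninth application is ignored.** The cycle is not defined in days, and assessment at every application does not exclude later assessment. Pharmacokinetic sampling runs to 40 hours after application, although the article does not say after which applications.
- **Later safety data are collected but not used.** The 4 to 9 weeks are not divided into phases, and the text describes no post-treatment visit. The extra time could be screening.
- **Late DLTs are lost and the MTD ends up too high.** The article says that a dose with an observed DLT must not be given again, and sets no time limit in that sentence. A DLT confirmed a few days late would still bar its dose.

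**Conclusion.** The point holds in a limited form. At the earliest time escalation is permitted, a grade 4 neutropenia that began in about the preceding 7 to 8 days is neither DLT nor TET, so the stated rules allow a higher dose before a DLT that would bar escalation can be determined. The consequence shown is premature exposure of up to three patients at the next level. A wrong final MTD is not shown.

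The result rests on the 3-week cycle from Table 1, which is firm, and on assumed dosing days, which move the dates but not the length of the gap. As a share of calendar days, the gap runs from 7/21 = 33% to 8/17 = 47%, with 7/19 = 37% for Monday/Wednesday/Friday dosing and k = 7. These are not probabilities of missing a DLT. They concern one DLT type in one to three patients per group, and without a neutropenia rate no probability can be given.

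**What to change.** Reconcile three statements under Dose escalation and extension: the DLT definition with its 7-day condition, the period over which DLTs count towards the MTD, and the condition for opening the next level. They should agree, so that DLT and TET status can be determined for every patient in the cohort before escalation. The revised text should also make clear how an episode counts if it begins within the cycle and passes 7 days afterwards. Which period and which visits achieve this is for the clinical team, and no waiting time is proposed here.

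The cost is a wording change and some added time per dose step. With at most 48 / 3 = 16 groups of three in the escalation part, any added interval would occur at most 16 times. Whether the total fits the planned duration of about two years cannot be judged from the article, because recruitment and screening times are not given. Nor can it be said whether extra visits are needed, since the article does not describe follow-up after treatment.
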